## Tumor imaging and assessment of disease

Besides the [^18^F]BMS-986192 and [^18^F]-FDG PET scans, a baseline MRI of head and neck will be made for baseline tumor measurements. Early response evaluation with MRI will be performed just before surgery (day 24 ±3, [Figure 1](#Figure1)). As included in standard of care, a diagnostic CT of neck, thorax and abdomen will be performed before treatment.

## Surgery

As described in section [3.6](#_Surgery).

## Adjuvant treatment

Adjuvant treatment (radiotherapy alone or in combination with chemotherapy or biotherapy with cetuximab) will be decided upon during the multidisciplinary board meetings, as indicated according to current guidelines. Treatment details will be registered and adverse events will be monitored.

## Follow-up visits

Visit requirements are outlined in section [7.19: Schedule of assessments](#_7.19_Schedule_of). Specific procedure-related details are provided above in [section 7: Study Procedures](#_STUDY_PROCEDURES). Subjects will have follow-up every 3 months until 12 months post-surgery, withdrawing consent, becoming lost to follow-up or the start of new anti-neoplastic therapy.

## Tissue sampling

Baseline tissue sampling will be obtained at panendoscopy, and a second tissue sampling will be obtained at surgey (after nivolumab treatment). Tumor tissue biopsies from the primary tumor and (affected) lymph nodes obtained at panendoscopy or surgical resection will be formalin fixed and fresh frozen .

When the [^18^F]BMS-986192 PET scan show heterogeneous uptake between tumor lesions in individual patients, or [^18^F]BMS-986192 PET and [^18^F]-FDG show discrepant results, up to two additional biopsies are allowed, if the area can be safely reached. If these discrepant results pertain to an area of interest that is already determined for surgical resection, a titanium marker is allowed to be placed before surgery under ultrasound guidance, if the area can be safely reached. The procedure for marker placement resembles that of taking a biopsy and holds similar risk.

## Screening period

During the short screening period (day -5 – 0) potential subjects will be evaluated to determine that they fulfill the entry requirements as set forth in [section 4](#_STUDY_POPULATION).

Written consent must be obtained prior to performing any protocol specific procedure. Results of a test performed prior to the subject signing consent as part of routine clinical management are acceptable in lieu of a screening test if performed within 30 days of study start, with the exception of laboratory test which should be performed within 14 days before study start. Screening procedures are to be completed prior to the first study procedure. Subjects may be rescreened after initially failing to meet the inclusion/exclusion criteria. Results from assessments performed during the initial screening period are acceptable in lieu of repeating a screening test if performed within the specified time frame and the results meet the inclusion/exclusion criteria. The screening period is estimated at 5 days, but may be elongated, only if standard of care procedures are delayed. Study procedures will not delay standard of care planning.

## Withdrawal/discontinuation

When a subject discontinues / withdraws prior to trial completion, all applicable activities scheduled for the final trial visit should be performed at the time of discontinuation. Any adverse events which are present at the time of discontinuation / withdrawal should be followed and assessed as described in [section 8](#_SAFETY_REPORTING).

### Withdrawal of individual subjects

Subjects may withdraw consent at any time for any reason or be dropped from the trial at the discretion of the investigator should any untoward effect occur. In addition, a subject may be withdrawn by the investigator if enrollment into the trial is inappropriate, the trial plan is violated, or for administrative and/or other safety reasons.

### Replacement of individual subjects after withdrawal

Subjects that fail to successfully undergo the PET scans will be replaced. In addition, in case baseline [^18^F]-FDG PET or diagnostic CT of neck, thorax and abdomen is suspicious for distant metastases the suspicious lesion will be biopsied. In case of proven metastases before the start of treatment with nivolumab, the patient will fall out of the study and will be replaced.

### Premature termination of the study

Early trial termination will be the result of the criteria specified below:

1. Incidence or severity of adverse drug reaction in this or other studies indicates a potential health hazard to subjects. Specifically, adverse events during treatment with nivolumab, during surgery and during standard adjuvant treatment (if indicated) will be monitored. In case of (prolonged) grade 4 or grade 5 toxicity, the investigators can temporarily halt the study for further analyses.

2. Quality or quantity of data recording is inaccurate or incomplete.

3. Poor adherence to the protocol and regulatory requirements.

## Schedule of assessments

|  |  | **Screening** | **Imaging I / Work-up** | | | | | | | | | **Panendoscopy** | | | **Nivolumab** | | **Check-up** | **Imaging II** | | **Surgery** | **3-monthly FU^1^** |
| --- | --- | --- | --- | --- | --- | --- | --- | --- | --- | --- | --- | --- | --- | --- | --- | --- | --- | --- | --- | --- | --- |
|  | Scheduling Window (days) | -5 – 0^11^ | 1 ±3 | | | | | | | | | 3 ±3 | | | 3±3 | | 13±3 | 24 ±3 | | 25 ±4 | >> |
|  | **Administrative Procedures** |  |  |  |  |  |  |  |  |  |  |  |  |  |  |  |  |  |  |  |  |
|  | Pre-screening Consent | X |  |  |  |  |  |  |  |  |  |  |  |  |  |  |  |  |  |  |  |
|  | Informed Consent | X |  |  |  |  |  |  |  |  |  |  |  |  |  |  |  |  |  |  |  |
|  | Elegibility Criteria | X |  |  |  |  |  |  |  |  |  |  |  |  |  |  |  |  |  |  |  |
|  | Demographics and Medical History | X |  |  |  |  |  |  |  |  |  |  |  |  |  |  |  |  |  |  | X |
|  | Prior and Concomitant Medication Review | X |  |  |  |  |  |  |  |  |  |  |  |  |  |  |  |  |  | X | X |
|  | **Imaging** |  |  |  |  |  |  |  |  |  |  |  |  |  |  |  |  |  |  |  |  |
|  | PET - [18F]-BMS-986192^2^ |  | X | | | | | | | | |  |  |  |  |  |  | X | |  |  |
|  | PET - [18F]-FDG^2^ | X | | | | | | | | | |  |  |  |  |  |  | X | |  |  |
|  | MRI Head-Neck | X |  | | | | | | | | |  |  |  |  |  |  | X | |  |  |
|  | Diagnostic CT-Neck-Thorax-Abdomen | X | | | | | | | | | |  |  |  |  |  |  |  |  |  |  |
|  | **Clinical Procedures/Assessments** |  |  |  |  |  |  |  |  |  |  |  |  |  |  |  |  |  |  |  |  |
|  | Directed Physical Examination | X |  |  |  |  |  |  |  |  |  |  |  |  | X | | X |  |  | X | X |
|  | Diagnostic Biopsy^3^ | X |  |  |  |  |  |  |  |  |  |  | | |  |  |  |  |  |  |  |
|  | Panendoscopy including biopsies |  |  |  |  |  |  |  |  |  |  | X | | |  |  |  |  |  |  |  |
|  | Review Adverse Events^4^ |  | X | | | | | | | | | X | | | X | | X | X | | X | X^5^ |
|  | Full Physical Examination | X |  |  |  |  |  |  |  |  |  |  |  |  |  |  |  |  |  |  | X |
|  | Vital Signs and Weight | X |  |  |  |  |  |  |  |  |  |  |  |  | X | |  |  |  | X | X |
|  | ECOG Performance Status | X |  |  |  |  |  |  |  |  |  |  |  |  | X | |  |  |  | X | X |
|  | MKA-OPT | X | | | | | | | | | |  |  |  |  |  |  |  |  |  |  |
|  | MKA extractions |  |  |  |  |  |  |  |  |  |  | X | | |  |  |  |  |  |  |  |
|  | Echo-FNAC | X | | | | | | | | | |  |  |  |  |  |  |  |  |  |  |
|  | Nivolumab treatment |  |  |  |  |  |  |  |  |  |  |  |  |  | X | |  |  |  |  |  |
|  | **Laboratory Procedures/Assessments** |  |  |  |  |  |  |  |  |  |  |  |  |  |  |  |  |  |  |  |  |
|  | Pregnancy Test^6^ | X |  |  |  |  |  |  |  |  |  |  |  |  |  |  |  |  |  |  |  |
|  | Complete Blood Count (CBC) | X |  |  |  |  |  |  |  |  |  |  |  |  |  |  | X |  |  | X | X |
|  | Comprehensive Serum Chemistry Panel^7^ | X |  |  |  |  |  |  |  |  |  |  |  |  |  |  | X |  |  | X | X |
|  | **Tumor Tissue and Blood collection** |  |  |  |  |  |  |  |  |  |  |  |  |  |  |  |  |  |  |  |  |
|  | Tissue collection for genomic profiling |  |  | | | | | | | | |  | | |  |  |  |  |  | X^8^ |  |
|  | Tissue collection for Immunohistochemistry |  |  | | | | | | | | | X^8^ | | |  |  |  |  |  | X^8^ |  |
|  | Tissue collection for flow cytometry |  |  | | | | | | | | |  | | |  |  |  |  |  | X^8^ |  |
|  | Blood for Immunophenotyping and plasma vesicle miRNA’s |  | X^9^ | | | | | | | | |  | | |  | | X | X^9^ | |  | X^10^ |
|  |  |  |  |  |  |  |  |  |  |  |  |  |  |  |  |  |  | |  |  |  |
|  | Standard of Care |  |  |  |  |  |  |  |  |  |  |  |  |  |  |  |  | |  |  |  |
|  | Study procedure |  |  |  |  |  |  |  |  |  |  |  |  |  |  |  |  | |  |  |  |

1. Follow up will end 12 months post-surgery, or earlier when withdrawing consent, becoming lost to follow-up or at the start of new anti-neoplastic therapy.
2. [^18^F]BMS-986192 PET and [^18^F]-FDG PET need to occur with an interval of min. 24h.
3. Only if diagnosis has not been histologically confirmed at presentation
4. This includes AEs, SAEs and SUSARs, as described in section 8.1
5. Adverse events will be monitored until 100 days after nivolumab treatment.
6. Only for women of childbearing potential.
7. This includes Albumin, Akaline phosphatase, Alanine aminotransferase (ALT), Aspartate aminotransferase (AST), Lactate dehydrogenase (LDH), Amylase, Lipase, Creatinine, Calcium, Glucose, Phosphorus, Potassium, Sodium, Chloride, Magnesium, Total Bilirubin, Free Thyroxine (T4), Triiodothyronine (T3), Thyroid Stimulating Hormone (TSH). 1 tube of 6ml EDTA (EK) and one tube of 6ml Heparin Gel (HG) need to be collected.
8. Tissues are collected during standard procedures.
9. Blood is to be withdrawn before [18F]-BMS-986192 administration.
10. For plasma vesicle miRNA analysis: blood collection at 1 and 3 months post-surgery as well as at time of progression of disease. For immunophenotyping 4x10ml has to be collected only once, at 3 months after surgery.
11. The screening period is estimated at 5 days, but may be elongated, only if standard of care procedures are delayed.

# SAFETY REPORTING

Section 10 WMO event

In accordance to section 10, subsection 1, of the Dutch law “Wet Medisch-wetenschappelijk Onderzoek (WMO)”, the investigator will inform the subjects and the reviewing accredited medical ethical committee (medische ethische toetsingscommissie, METC) if anything occurs, on the basis of which it appears that the disadvantages of participation may be significantly greater than was foreseen in the research proposal. The study will be suspended pending further review by the accredited METC, except insofar as suspension would jeopardise the subjects’ health. The investigator will take care that all subjects are kept informed.

## AEs, SAEs and SUSARs

### Adverse events (AEs)

Adverse events are defined as any undesirable experience occurring to a subject during the study, whether or not considered related to radioactive tracers or nivolumab treatment. An investigator who is a qualified physician will evaluate all adverse events according to the NCI Common Terminology for Adverse Events (CTCAE), version 5.0. Any adverse event which changes CTCAE grade over the course of a given episode will have each change of grade recorded on the adverse event case report forms/worksheets.

All adverse events regardless of CTCAE grade must also be evaluated for seriousness.

### Serious adverse events (SAEs)

A serious adverse event is any untoward medical occurrence or effect that at any dose:

- results in death;
- is life threatening (at the time of the event);
- requires hospitalisation or prolongation of existing inpatients’ hospitalisation;
- results in persistent or significant disability or incapacity;
- is a congenital anomaly or birth defect;
- Any other important medical event that may not result in death, be life threatening, or require hospitalization, may be considered a serious adverse experience when, based upon appropriate medical judgement, the event may jeopardize the subject or may require an intervention to prevent one of the outcomes listed above.
- Potential drug induced liver injury (DILI) is also considered an important medical event.
- Complications during or after surgical procedures and during adjuvant treatment are also considered an important medical event.
- Suspected transmission of an infectious agent (e.g., pathogenic or nonpathogenic) via the study drug is an SAE.

Although pregnancy, overdose, and cancer are not always serious by regulatory definition, these events must be handled as SAEs.

### Suspected Unexpected Serious Adverse Reactions (SUSARs)

Adverse reactions are all untoward and unintended responses to an investigational product related to any dose administered.

Unexpected adverse reactions are SUSARs if the following three conditions are met:

1. the event must be serious;
2. there must be a certain degree of probability that the event is a harmful and an undesirable reaction to nivolumab, regardless of the administered dose;
3. the adverse reaction must be unexpected, that is to say, the nature and severity of the adverse reaction are not in agreement with the product information as recorded in the Investigator Brochure [32].

The sponsor will report expedited the following SUSARs through the web portal *ToetsingOnline* to the METC:

- SUSARs that have arisen in the clinical trial that was assessed by the METC;
- SUSARs that have arisen in other clinical trials of the same sponsor and with the same medicinal product, and that could have consequences for the safety of the subjects involved in the clinical trial that was assessed by the METC.

The remaining SUSARs are recorded in an overview list (line-listing) that will be submitted once every half year to the METC. This line-listing provides an overview of all SUSARs from the two investigational products (PET tracer and nivolumab), accompanied by a brief report highlighting the main points of concern.

The expedited reporting of SUSARs through the web portal ToetsingOnline is sufficient as notification to the competent authority.

The sponsor will report expedited all SUSARs to the competent authorities in other Member States, according to the requirements of the Member States.

The expedited reporting will occur not later than 15 days after the sponsor has first knowledge of the adverse reactions. For fatal or life threatening cases the term will be maximal 7 days for a preliminary report with another 8 days for completion of the report.

### Potential Drug Induced Liver Injury (DILI)

Wherever possible, timely confirmation of initial liver-related laboratory abnormalities should occur prior to the reporting of a potential DILI event. All occurrences of potential DILIs, meeting the defined criteria, must be reported as SAEs. Potential drug induced liver injury is defined as:

1. ALT or AST elevation > 3 times upper limit of normal (ULN)

AND

1. Total bilirubin > 2 times ULN, without initial findings of cholestasis (elevated serum alkaline phosphatase)

AND

1. No other immediately apparent possible causes of AST/ALT elevation and hyperbilirubinemia, including, but not limited to, viral hepatitis, pre-existing chronic or acute liver disease, or the administration of other drug(s) known to be hepatotoxic.

### Laboratory Test Abnormalities

All laboratory test results captured as part of the study should be recorded following institutional procedures. Test results that constitute SAEs should be documented and reported as such.

The following laboratory abnormalities should be documented and reported appropriately:

- any laboratory test result that is clinically significant or meets the definition of an SAE
- any laboratory abnormality that required the subject to have study drug discontinued or interrupted
- any laboratory abnormality that required the subject to receive specific corrective therapy.

Progression of the cancer under study is not considered an adverse event unless it results in hospitalization or death.

### Complications during surgery

In recent studies administration of neoadjuvant nivolumab is associated with few side effects during surgery. In a cohort of 22 NSCLC patients, scheduled for surgical resection, patients received two two-weekly doses of 3 mg/kg nivolumab. No previously unreported toxic effects were observed. Treatment-related adverse events occurred in 5 of 22 patients, with only one grade 3 event (pneumonia). Furthermore, neoadjuvant nivolumab did not cause treatment-related surgical delays [30]. A similar study in HNSCC included 29 HNSCC patients eligible for surgical resection. Patients received 240 mg nivolumab on day 1 and on day 15 of the study, and surgery was performed on day 29±7. Preliminary results were presented at EMSO in 2017 [68]. No new safety signatures were defined. Grade 3-4 treatment-related adverse events occurred in 4 patients and consisted of glossodynia and lipase increase.

Based on these studies we do not expect any complications of special interest during surgery or adjuvant treatment.

## Serious Adverse Event Collection and Reporting

Following subject’s written consent to participate in the study, all SAEs, whether related or not related to one of the radioactive tracers, study procedure or nivolumab, must be collected, including those thought to be associated with protocol-specified procedures. All SAEs must be collected that occur within 100 days of discontinuation of dosing or the initiation of new anti-cancer therapy, whichever is earlier.

All SAEs must be collected that occur during the screening period. If applicable, SAEs must be collected that relate to any protocol-specified procedure (eg, additional tumor biopsy, PET scans). The investigator should report any SAE that occurs after these time periods that is believed to be related to nivolumab or protocol-specified procedures.

SAEs, whether related or not related to one of the radioactive tracers, study procedure or nivolumab, and pregnancies must be reported to BMS at the same time when reporting to METC within 24 hours. SAEs will be reported through the web portal *ToetsingOnline* to the accredited METC that approved the protocol.

SAEs must be recorded on a **SAE** form and pregnancies on a Pregnancy Surveillance Form via:

**SAE Email Address:**  [contact]

**SAE Facsimile Number: +1** [contact]

If only limited information is initially available, follow-up reports are required. (Note: follow-up SAE reports should include the same investigator term(s) initially reported.)

If an ongoing SAE changes in its intensity or relationship to nivolumab or if new information becomes available, a follow-up SAE report should be sent within 24 hours to BMS (or designee) using the same procedure used for transmitting the initial SAE report.

All SAEs should be followed to resolution or stabilization.

The Sponsor/Investigator (VUmc) will ensure that all SAEs in the clinical database are reported to BMS and any applicable health authority during the conduct of the study including periodic reconciliation.

VUmc shall ensure that all Study Personnel (including Investigator) report to BMS all adverse events and other reportable events in the course of the Study in accordance with Applicable Law and the Protocol. VUmc shall ensure that Study Personnel (including Investigator) perform case level reconciliation to confirm BMS has received all reports reported by Study Personnel. Study Personnel shall use the form of reconciliation report requested by BMS and shall e-mail all reconciliation reports to [contact]

Reconciliation shall be performed on a quarterly basis, unless otherwise agreed by BMS in writing.

All Study Personnel (including Investigator) shall complete any training reasonably requested by BMS relating to safety reporting, and shall provide evidence of, or certify to, the same, as reasonably requested by BMS.

## Pregnancy

If, following treatment with nivolumab, it is subsequently discovered that a study subject is pregnant or may have been pregnant at the time of investigational product exposure, including during at least 6 half-lives after product administration, the investigational product will be permanently discontinued.

The investigator must immediately notify [contact] of this event via the Pregnancy Surveillance Form in accordance with SAE reporting procedures.

Follow-up information regarding the course of the pregnancy, including perinatal and neonatal outcome and, where applicable, offspring information must be reported on the Pregnancy Surveillance Form (provided upon request from BMS)

Any pregnancy that occurs in a female partner of a male study participant should be reported to BMS. Information on this pregnancy will be collected on the Pregnancy Surveillance Form.

## Overdose

An overdose is defined as the accidental or intentional administration of any dose of a product that is considered both excessive and medically important. All occurrences of overdose must be reported as an SAE.

## Other safety considerations

Any significant worsening noted during interim or final physical examinations, electrocardiograms, x‑rays, and any other potential safety assessments, whether or not these procedures are required by the protocol, should also be recorded as a nonserious or serious AE, as appropriate, and reported accordingly.

## Annual safety report

In addition to the expedited reporting of SUSARs, the sponsor will submit, once a year throughout the clinical trial, a safety report to the accredited METC, competent authority, and competent authorities of the concerned Member States.

This safety report consists of:

- a list of all suspected (unexpected or expected) serious adverse reactions, along with an aggregated summary table of all reported serious adverse reactions, ordered by organ system, per study;
- a report concerning the safety of the subjects, consisting of a complete safety analysis and an evaluation of the balance between the efficacy and the harmfulness of the medicine under investigation.

## Follow-up of adverse events

All AEs will be followed until they have abated, or until a stable situation has been reached, up until 100 days after administration of nivolumab. Depending on the event, follow up may require additional tests or medical procedures as indicated, and/or referral to the general physician or a medical specialist.

SAEs need to be reported till end of study within the Netherlands, as defined in the protocol.

# STATISTICAL ANALYSIS

## Analysis of PET data

SUV_max_, SUV_mean_ and SUV_peak_ (both tracers) will be measured for all tumor lesions and enlarged lymph nodes. For ^18^F-FDG also MTV and TLG will be determined.

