## Analysis of PET data

### [18F]BMS-986192 PET

All PET data will be normalized and corrected for randoms, tissue attenuation, decay, scatter and dead time. PET-CT data will be reconstructed with TF-OSEM, resulting in a transaxial spatial resolution of ~7 mm in the centre of the field of view. Volumes of interest (VOIs) will be defined using the CT images which are co-registered to the PET-CT data and using a threshold technique [59, 65, 66]. The maximum pixel value within the tumor (SUV_max_), the 3D SUV_peak_, a threshold defined volume of interest providing SUV_mean_ and a manually CT defined volume (SUV_CT_) will be derived for any lesion with adequate focal uptake (50-53).

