# ENDPOINTS

## Main study parameters/endpoints

PET Imaging

[^18^F]BMS-986192 and [^18^F]-FDG SUV_max_, SUV_mean,_ SUV_peak_ will be measured in all tumor lesions and (enlarged) lymph nodes using manually drawn volumes of interest (VOI) before and on treatment. For [^18^F]BMS-986192 manually drawn VOIs will also be calculated for liver, kidneys, lungs, spleen and left ventricle of the heart.

(Serious) adverse events

We will pay special interest to all adverse events during the study, in order to obtain information on safety and tolerability of neoadjuvant nivolumab in patients with locally advanced oral cancer who are planned for treatment with curative intent including surgery.

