## Secondary study parameters/endpoints

#### Heterogeneity analysis

#### Interpatient, intrapatient and intratumor SUV heterogeneity.

Correlation between both PET scans, and between imaging and response

The correlation between SUV for [^18^F]BMS-986192 and [^18^F]-FDG baseline and on treatment and early response evaluation with [^18^F]-FDG.

Correlation between PET data and Blood/Tissue markers

The correlation between continuous values as SUV and the categorical variables tissue PD-1 and PD-L1 IHC will be assessed for each tumor lesion. Correlation with immuno-monitoring analysis in tumor tissue/lymph nodes and blood, plasma vesicle miRNAs from blood, as well as DNA/RNA profiling in tumor tissue at baseline and at surgery will be assessed.

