### Intrapatient heterogeneity

Tracer uptake differences between lesions of the same patient depend on multiple aspects. These are both biological (e.g. the level of perfusion and target expression), as well as technical (e.g. partial volume and tumor motion effects). True biological differences between lesions that correlate with tumor biology are therefore difficult to define. Because of this, intrapatient uptake differences will be assessed qualitatively.

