## Correlation between PET data and response

The correlation between the continuous variable SUV, the % change in SUV and TLG and the categorical variables response on imaging (according to RECIST 1.1 CR, PR, SD, PD and CMR, PMR, SMD and PMD according to PERCIST) and pathological response (according to the Mandard Classification System, Table 3) will be assessed.

**Table 3** Mandard Classification system for Tumor Regression Grading (TRG) [69, 70]

| **Descriptive** |  |  |
| --- | --- | --- |
| Complete regression | TRG 1 | No residual cancer cells |
| Subtotal | TRG 2 | Rare cancer cells |
| Partial | TRG 3 | Fibrosis outgrowing residual cancer |
| No regression | TRG 4 | Residual cancer outgrowing fibrosis |
|  | TRG 5 | Absence of regressive change |

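### Section 9.2.2 treats lesion SUV cautiously because of partial-volume effects, but the change, BMS-FDG and IHC analyses use the same uncorrected SUVs without it, so lesions below about 25 mm can yield size-driven correlations

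*Protocol*

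**What the plan says.** Section 5.5.1 describes a reconstruction "resulting in a transaxial spatial resolution of ~7 mm in the centre of the field of view". Its correction list reads "All PET data will be normalized and corrected for randoms, tissue attenuation, decay, scatter and dead time"; partial volume is not in it. The entry rule there concerns uptake, not size: SUV measures "will be derived for any lesion with adequate focal uptake".

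Section 6.1 (main endpoint) says SUVs "will be measured in all tumor lesions and (enlarged) lymph nodes using manually drawn volumes of interest (VOI) before and on treatment". Section 9.1 repeats that they "will be measured for all tumor lesions and enlarged lymph nodes".

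Section 9.2.2 lists among the causes of differences between lesions of one patient "technical (e.g. partial volume and tumor motion effects". It concludes that true biological differences are hard to define and that this comparison will be qualitative.

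Three other analyses use the same SUVs as numbers:

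- Section 9.3 assesses "The correlation between the continuous variable SUV, the % change in SUV and TLG and the categorical variables response on imaging" (RECIST 1.1 and PERCIST) and Mandard grade.
- Section 6.2, under "Correlation between both PET scans, and between imaging and response", relates BMS-986192 SUV to FDG SUV at baseline and on treatment. Objective 3 in section 2.2 extends this to changes in FDG uptake.
- Section 9.4 compares SUV across PD-1 and PD-L1 IHC categories by ANOVA.

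None of these carries a size limit, a size term or the caution of section 9.2.2.

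**The concern.** At about 7 mm resolution a small lesion shows less SUV than it truly has, and the loss grows as diameter falls. A small lesion that shrinks therefore loses measured SUV even if PD-L1 expression and metabolism have not changed. Three consequences follow:

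- RECIST response is itself shrinkage. SUV fall and RECIST response can move together for a purely geometric reason.
- Both tracers are scaled by the same recovery factor in the same lesion. Their changes can correlate when uptake of both is constant.
- Section 1.2.2 expects FDG uptake to rise early in responders. The artefact lowers SUV in shrinking lesions, so it can also hide that signal.

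The trial is meant to pick biomarkers for a larger randomised trial (section 1.1.2). A correlation produced by lesion size would misdirect that choice, and more patients would not remove it.

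**Working it through.** The protocol states no figure for this effect, so there is none to reproduce.

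**Inputs from the protocol.** Resolution about 7 mm (5.5.1); no partial-volume correction (5.5.1); no minimum size (6.1, 9.1); 15 evaluable patients (4.3); a 15% SUV difference counted as real between patients, from test-retest variability (9.2.1). The 15% is not set as a threshold for change and serves here only as a yardstick.

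**Assumptions.** Uniform spherical lesion; isotropic Gaussian blur of 7 mm FWHM; background b of 0 to 25% of lesion activity; 1 ml sphere for SUVpeak; 30% example shrinkage; lesion diameters, which the protocol does not give.

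**Recovery at the lesion centre (noise-free SUVmax).** With σ = 7/2.3548 = 2.97 mm and x = radius/σ:

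RC = erf(x/√2) − √(2/π)·x·exp(−x²/2)

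- 20 mm: x = 3.36, RC = 0.999 − 0.009 = 0.990
- 14 mm: x = 2.355, RC = 0.981 − 0.117 = 0.864

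A 20 to 14 mm shrinkage gives 0.864/0.990 = 0.873, a fall of 12.7%. With background the measured fraction is b + (1 − b)·RC. At b = 0.25 the ratio is 0.898/0.992 = 0.905, a fall of 9.5%.

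**SUVpeak.** Averaging the blurred profile over 1 ml gives recovery of 0.588 at 14 mm and 0.900 at 20 mm (b = 0). The fall is 1 − 0.588/0.900 = 34.7%. At b = 0.25 it is 1 − 0.691/0.925, about 25%.

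| Diameter, 30% fall | SUVmax, b = 0 / 0.25 | SUVpeak, b = 0 / 0.25 |
|---|---|---|
| 20 to 14 mm | −12.7% / −9.5% | −34.7% / −25% |
| 25 to 17.5 mm | −3.4% / −2.5% | −18.5% / −14% |
| 30 to 21 mm | −0.6% / −0.4% | −7.1% / −5% |

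At b = 0.20 the fall drops below 15% from baseline diameters of about 18.5 mm (SUVmax), 25 mm (SUVpeak), 21 mm (SUVmean in a 50% isocontour) and 20 mm (CT-outlined mean). The two means still lose about 8 to 9% at 30 mm. For a 20 mm lesion, FWHM of 6 to 8 mm moves the SUVpeak fall from 24 to 30% and the SUVmax fall from 4 to 17%.

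**Correlations with no true relation.** 1,500 simulated sets of 15 lesions; b = 0.20; diameter change uniform from −40% to +10%; 10% noise per change; independent tracer uptakes with log SD 0.4. Ranges span the four SUV measures.

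| Lesion diameters | SUV change vs diameter change | BMS change vs FDG change | Baseline BMS vs FDG |
|---|---|---|---|
| 8–20 mm | 0.72–0.84 | 0.60–0.81 | 0.14–0.37 |
| 8–40 mm | 0.47–0.62 | 0.51–0.74 | 0.18–0.42 |
| 15–40 mm | 0.26–0.49 | 0.30–0.64 | 0.01–0.05 |
| 25–50 mm | 0.03–0.35 | 0.01–0.15 | about 0 |

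**Against response categories, as section 9.3 plans.** Each lesion was classed at assumed cut-offs of −30% and +20% and compared by Kruskal-Wallis. Diameter change had mean −10% and SD 20%, with 12.5% noise and uptake constant. The share of runs with p < 0.05 (nominal 5%) was:

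- 12–25 mm: about 50 to 56% for SUVpeak, 26 to 31% for SUVmax
- 20–40 mm: about 16 to 22% and 4 to 7%
- 25–50 mm: about 6 to 9% and 3%

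**Baseline BMS-FDG at the protocol's own spread.** Section 1.1.4 reports tracer SUV 3.4 (±2.9). If ± is an SD and uptake is lognormal, the log SD is √ln(1 + (2.9/3.4)²) = √ln 1.73 = 0.74. With 15 primaries of 25–50 mm, 30 nodes of 10–25 mm, that BMS spread and an FDG log SD of 0.3 to 0.74, the mean r between unrelated tracers is 0.05–0.19 for SUVpeak and 0.01–0.04 for SUVmax.

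**SUV against IHC.** At b = 0.20 SUVpeak recovery is 0.44 at 10 mm and 1.00 at 30 mm. Two lesions with equal uptake would differ by a factor of 1.00/0.44 = 2.3.

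**The case against.** **A statistical analysis plan may cover this.** Size limits and sensitivity analyses often sit there, and section 9.3 names no test. That is fair. But the protocol itself raises partial volume, draws a consequence for one comparison, and does not carry it to the others. That inconsistency stands whatever another document adds.

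**The lesions may be large.** The population has stage III/IV disease needing resection and flap reconstruction, and nodes must be enlarged. If most lesions are 30 mm or more, little remains. This stands, and it is why the magnitude is conditional. However, lymph nodes belong to primary objective 1, and section 1.1.2 cites shrinkage in 40 to 50% of patients in a similar setting.

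**The study is descriptive (section 4.3).** No decision rule depends on these correlations. This limits the harm to misreading, but the correlations are what the pilot will pass on.

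**Stronger readings that the documents do not support.**

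- A reader might infer that the plan ignores lesion size altogether. Section 9.2.2 shows otherwise and already protects the comparison of small nodes with the primary tumor.
- A reader might infer that shrinkage always lowers SUV, or that false associations are near certain. Correlating SUV change with continuous diameter change does give p < 0.05 in 75 to 98% of runs for 12–25 mm lesions. Section 9.3 uses categories, where the rates are those above.
- A reader might expect the artefact to favour the imaging hypothesis. For FDG it runs against it.
- Mandard grade is histological, so its link to lesion size is only indirect.

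**Conclusion.** The point holds in conditional form. The protocol accepts that partial volume distorts lesion SUV, yet uses the same uncorrected SUVs quantitatively in sections 9.3, 9.4 and 6.2. For lesions below about 25 mm, shrinkage alone can move SUVpeak by 15% or more and create an apparent link with RECIST response or between the two tracers' changes. It can equally mask an FDG rise. For lesions of 30 mm or more the effect is negligible for SUVmax, small for SUVpeak, and a residual 8 to 9% for the volume means. Baseline BMS-FDG inflation is small unless many lesions are below about 15 mm. All of this rests on assumed lesion sizes, spherical uniform lesions and a Gaussian 7 mm blur; real SUVmax is also noisier than the model's.

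**What to change.** - **Section 9.1:** report each lesion's MRI or CT diameter beside its SUV at both scans.
- **Section 9.3:** keep all lesions in the main analysis. Add a pre-stated repeat of % change in SUV against RECIST, and of BMS change against FDG change, in lesions of at least 25 mm at baseline, with 30 mm as a further check. Show SUVmax beside SUVpeak. The 30 mm check matters because a 14 to 19% SUVpeak fall is still possible at 25 mm.
- **Baseline BMS-FDG and SUV-IHC (6.2, 9.4):** add an analysis of log SUV adjusted for log diameter at the same scan.
- **Do not adjust for diameter where RECIST or Mandard grade is the outcome.** Shrinkage is the RECIST outcome itself and may lie on the pathway to pathological response.
- **Interpretation:** state that a correlation seen only in small lesions will not be read as a biomarker signal.

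Cost: some wording and analysis work. Head-and-neck MRI is already planned at baseline and before surgery (3.5, 7.12). The restricted repeat may contain few lesions in a 15-patient study, so it serves as a check beside the main analysis and does not replace it.
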